Phase 1: adaptation	1–2	Restore motor control and neuromuscular adaptation	Deep trunk stabilizers, scapular stabilizers, hip stabilizers	Low-load, bilateral, predominantly single-joint exercises; low coordination demand	2–3 sets; 10–12 reps RPE 3–4	≥80% session completion; pain ≤3/10; RPE ≤ 4; No symptom worsening within 24 h
Phase 2: load introduction	3–4	Develop basic strength and joint stability	Shoulder complex; wrist stabilizers; lumbopelvic region	Bilateral multi-joint exercises; increased ROM and core engagement	2–3 sets; 12–15 reps; RPE 4–5	≥80% adherence; Average RPE ≤ 5; No adverse events
Phase 3: dynamic stability and unilateral control	5–6	Enhance dynamic stability and unilateral neuromuscular control	Rotator cuff, scapulothoracic musculature, hip abductors and extensors	Unilateral multi-joint exercises; increased balance and coordination demands	3 sets; 8–12 reps; RPE 5–6	≥80% Adherence; RPE 5–6 without excessive fatigue; Positive tolerance feedback
Phase 4: functional integration and movement efficiency	7–8	Integrate strength into functional movement patterns	Upper limb–trunk–hip kinetic chain	Functional, task-oriented multi-joint exercises; higher coordination, control, and movement efficiency demands	3 sets; 8–10 reps; RPE 6–7	≥80% adherence; RPE ≤ 7; Self-reported readiness to progress

All participants will receive an exercise kit designed to facilitate the completion of home-based sessions, including elastic bands of different resistance levels, an exercise mat, a foam roller, and massage balls.

Adherence to the intervention will be monitored using attendance records for face-to-face workshops and usage data from the RehBody application. Participants will be considered adherent if they attend at least 80% of the planned sessions. This adherence threshold will be used to define the per-protocol sample for the primary analysis.

TIDieR alignment: The intervention description follows the TIDieR checklist, specifying what, who, how, where, when, how much, and individualization/progression.

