#### Primary outcome

2.6.2

*Pain intensity:* Pain intensity will be measured using the Numeric Rating Scale (NRS), an 11-point validated self-reported measure widely used in musculoskeletal and occupational health research. Participants will be asked to rate their average musculoskeletal pain on a scale ranging from 0 (no pain) to 10 (worst imaginable pain) during face-to-face assessment sessions.

The NRS has demonstrated good reliability, validity, and responsiveness to change in musculoskeletal populations. Scores are commonly interpreted as: mild pain (1–3), moderate pain (4–6), and severe pain (7–10) (17).

The MCD for the NRS in musculoskeletal pain has been estimated at 1.5–2 points, which will be used to interpret the clinical relevance of pre–post changes (18). The primary outcome will be the change in NRS scores from baseline to post-intervention.

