### Sample size

2.9

Based on previous studies conducted in industrial worker populations evaluating similar interventions, a minimum clinically important difference of 1.5 points on the NRS for pain was assumed, together with a standard deviation of 2.5 points (36, 37). Using a two-sided *α* level of 0.05 and a statistical power of 80%, the required sample size for a paired-sample comparison was estimated to be 27 participants (Cohen’s d = 0.60). Accounting for an anticipated 20% attrition rate, the final adjusted target sample size was set at 33 participants. The computation was performed using Jamovi (version 2.7.6; www.jamovi.org), specifically the power analysis module for paired-sample *t*-tests.

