### Statystical analysis

2.10

The statistical analysis of the quantitative data will be performed using IBM-SPSS Statistics version 29 (IBM Corp., Armonk, NY, United States). Data will be expressed as the mean and the standard deviation with a 95% confidence interval or as the median and the interquartile range. The Shapiro–Wilk test will be used to assess normality.

Given the longitudinal design with three assessment points (baseline, post-intervention, and one-month follow-up), changes over time will be analysed using repeated-measures analysis. When parametric assumptions are met, a repeated-measures ANOVA will be conducted, with post-hoc pairwise comparisons adjusted using the Bonferroni correction.

For non-parametric data, the Friedman test will be used to assess overall changes over time, with post-hoc pairwise comparisons conducted using Wilcoxon signed-rank tests, and *p*-values adjusted using the Bonferroni correction.

Effect sizes and 95% confidence intervals will be reported to quantify the magnitude of observed changes, using eta squared (η^2^) for ANOVA analyses and Kendall’s W for Friedman tests, in addition to *p*-values.

The primary analysis will follow a per-protocol approach, including only participants who attended at least 80% of the planned intervention sessions, as defined by the adherence criteria.

Statistical significance will be set at *p* < 0.05.

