### Strengths and limitations of this study

3.1

This study describes a workplace-embedded, multimodal intervention combining health education and a digitally supported exercise program, specifically designed for textile manufacturing workers, which enhances ecological validity and real-world applicability.

The absence of a control group was a pragmatic decision driven by contextual and organizational constraints of the workplace setting. The intervention was implemented at the company level during working hours, and randomization of workers or staggered (stepped-wedge) implementation was not feasible due to production requirements, shift organization, and the company’s preference to offer the program equally to all interested employees. Therefore, a single-arm pre–post design was considered the most appropriate approach for this preliminary evaluation.

The hybrid delivery model (face-to-face workshops plus app-based exercise) may improve accessibility, adherence and scalability of musculoskeletal health promotion programs in industrial settings with time and workload constraints.

The use of validated outcome measures across physical, psychosocial and work-related domains allows a comprehensive evaluation of intervention effects beyond pain alone.

The quasi-experimental pre–post design without a control group limits causal inference and does not account for potential temporal or external confounding factors.

The relatively small sample size and single-center recruitment may limit the generalizability of the findings to other occupational sectors or industrial contexts.

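### The primary pain analysis is restricted to participants with at least 80% attendance, a post-enrolment selection that may bias the result and for which the sample size makes no allowance

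*Protocol article*

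**What the plan says.** Section 2.10 of the protocol article (headed Statystical analysis) fixes the primary set: "The primary analysis will follow a per-protocol approach, including only participants who attended at least 80% of the planned intervention sessions". Section 2.5.2 (App-based exercise program) says the same: "This adherence threshold will be used to define the per-protocol sample for the primary analysis". The article names no other analysis set.

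The design is single-arm and pre-post (section 2.1). The endpoint is within-person: "The primary outcome will be the change in NRS scores from baseline to post-intervention" (section 2.6.2).

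Section 2.9 sizes the study for a paired comparison: "a minimum clinically important difference of 1.5 points on the NRS for pain was assumed", "together with a standard deviation of 2.5 points", 80% power, giving d = 0.60 and 27 participants. It then adds one allowance: "Accounting for an anticipated 20% attrition rate, the final adjusted target sample size was set at 33 participants". No expected adherence rate is given. Section 2.7.1 lists adherence and retention as separate feasibility indicators.

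The Introduction presents the programme as a feasible and scalable approach. Section 3.1 says of the intervention's workplace setting: "which enhances ecological validity and real-world applicability".

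**The concern.** Membership of the primary set is decided by behaviour during the eight weeks in which pain is expected to change. Table 1 makes progression depend on pain, perceived exertion, symptom worsening or tolerance, depending on the phase, so a link between how a worker is doing and how many sessions are completed is credible. A worker whose pain worsens may do fewer sessions and so leave the primary analysis.

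A single-arm design has no comparator to show how much of the observed change comes from this selection. Section 3.1 acknowledges the missing control group and external confounding, but not this mechanism.

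The estimand also shifts. The result describes workers who managed at least 80% of sessions, whereas the stated interest is a programme that works in an ordinary workplace. The Discussion itself names low worker adherence and lack of time during shifts as barriers. Workers who meet those barriers are the ones most likely to be excluded.

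Finally, completers who fall below the threshold reduce the analysed number, and the sample size makes no provision for them.

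**Working it through.** **Inputs from section 2.9:** difference 1.5, SD 2.5, two-sided alpha 0.05, power 80%, required n 27, attrition 20%, target 33. Because 1.5/2.5 = 0.60 is used in a paired test, 2.5 is taken as the SD of the change.

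**Assumptions, not in the documents:** the share p of completers who meet the 80% rule, and the correlation rho between adherence propensity and improvement. Both are shown as ranges.

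**1. The plan's own figure.** Exact paired t-test power uses the noncentral t with n − 1 degrees of freedom and noncentrality 0.60 × √n.
- n = 24 gives 80.4%, so 24 pairs suffice for 80% power.
- n = 27 gives 85.1%. The stated 27 is not reproduced at 80%; it is the n for 85%.

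**2. Attrition step.** 27 × 1.2 = 32.4, rounded up to 33. Dividing instead, 27/0.8 = 33.75, rounded up to 34. With 33 enrolled, 33 × 0.8 = 26.4, so 26 remain, with 83.6% power. This one-person shortfall comes from multiplying rather than dividing, not from the attendance rule.

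**3. Effect of the attendance rule on n and power.** n = 26.4 × p, rounded down:

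| Completers meeting the rule (assumed) | n analysed | Power at d = 0.60 |
|---|---|---|
| 100% | 26 | 83.6% |
| 90% | 23 | 79% |
| 80% | 21 | 74% |
| 70% | 18 | 67% |
| 60% | 15 | 58% |

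Power is below 80% only when fewer than 24 are analysed. That means adherence below 24/26.4 = 91% of completers at 20% attrition, or fewer than 24/33 = 73% of those enrolled both retained and adherent. The planned 27 is reached if at least 27 of 33 (82%) are both retained and adherent.

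**4. Selection shift.** Suppose the true mean change is 0 and the fraction p with the highest adherence propensity is kept. Under bivariate normality the apparent mean gain is rho × 2.5 × φ(z)/p, where z is the cut-off that keeps p.
- p = 0.8: φ(z)/p = 0.280/0.8 = 0.350.
- p = 0.6: φ(z)/p = 0.386/0.6 = 0.644.

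The false-positive rate is the probability that the two-sided 5% paired t-test rejects at that shift, with n = 21 or 15 from step 3 and the SD held at 2.5.

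| rho (assumed) | Gain, 80% kept | False-positive rate, n = 21 | Gain, 60% kept | False-positive rate, n = 15 |
|---|---|---|---|---|
| 0 | 0 | 5.0% | 0 | 5.0% |
| 0.1 | 0.09 | 5.3% | 0.16 | 5.6% |
| 0.3 | 0.26 | 7.4% | 0.48 | 10.7% |
| 0.4 | 0.35 | 9.4% | 0.64 | 15.4% |

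Against the 1.5-point planning difference, the largest shift is 0.64/1.5 = 43%. A negative correlation would give shifts of the same size in the opposite direction.

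**The case against.** **Direction of bias.** A reader might infer that the result is bound to be biased towards benefit. The documents do not support that. They report no link between attendance and pain response. They offer other reasons for missed sessions: time within shifts, production requirements and shift organisation. Section 2.5.2 adapts exercises to tolerance, which weakens the route through discomfort. Workers whose pain resolves might also stop, which would reverse the sign. At zero correlation there is no bias. So a plausible bias stands; a certain one does not.

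**Shortfall.** A reader might also infer that the analysed number must fall below 27 because of the attendance rule. It need not: no adherence rate is given, and the drop to 26 has another cause (step 2). The 27 carries about 85% power, so a modest loss is absorbed; at 90% adherence power is still 79%. Section 2.9 does not define attrition. Listing adherence and retention separately suggests that non-adherence is not included, but that is an inference.

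**Purpose.** Attendance, app adherence and retention will be reported, so poor uptake would be visible. The study calls itself preliminary and concedes limited causal inference. The phrase on real-world applicability describes the intervention, not the analysis. This softens the conflict with purpose but does not change whom the primary estimate describes.

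**Other sets and follow-up.** The article condenses a fuller plan, so its silence does not show that no all-participant analysis is planned. Nor does it show that low attenders are lost to assessment: sections 2.1 and 2.8 plan reassessment after the intervention and at one month, with no stop for low attendance. The choice of primary set, however, is stated twice, and adding a supportive analysis elsewhere would not alter it.

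**Conclusion.** The point holds as a criticism of the primary analysis set. Sections 2.5.2 and 2.10 condition the headline NRS change on post-enrolment attendance in a design with no comparator. The estimate applies to compliers and may be biased, plausibly towards benefit.

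Under the assumed correlations of 0 to 0.4 and 60% to 80% kept, the apparent gain with no true effect is 0 to 0.64 points and the false-positive rate 5% to about 15%. These figures are illustrations, since the documents supply neither quantity.

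The sample-size part is secondary and conditional. Non-adherence has no allowance of its own, and power would be 58% to 79% if 60% to 90% of completers met the rule at the planned attrition. The stated 80% is kept as long as at least 24 are analysed. The selection problem remains even if the numbers turn out to be sufficient.

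**What to change.** In section 2.10, define the primary analysis set as all enrolled participants with a baseline NRS, regardless of attendance. Estimate the baseline-to-post-intervention change from a model that uses all available visits. Move the 80% per-protocol set to a sensitivity analysis, and amend the matching sentence in section 2.5.2. Confirm in section 2.8 that the T1 and T2 assessments already planned apply to low attenders too.

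The cost is a paragraph of wording and, at most, some effort to assess low attenders, who are employees at the site. No larger sample is needed on the plan's own effect size: 26 analysed gives 83.6% power and all 33 would give 91.6%. The downside is that the estimated mean change may be smaller, and power with it, because non-attenders are included; that is the relevant estimate for workers offered the programme.

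If the sponsor keeps the per-protocol set as primary, the sample size should cover attrition and non-adherence together. Enrolment is then 27/(0.8 × p): 38, 43, 49 or 57 at an assumed p of 90%, 80%, 70% or 60%. To hold only the 24 needed for 80% power, it is 24/(0.8 × p): 34, 38, 43 or 50. This restores power but leaves the selection in place.

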Against this background, workplace-embedded multimodal programs that deliver both onsite health education and supervised exercise, together with home-based exercise supported by a digital app, may represent a feasible and scalable strategy to address MSD burden in manufacturing environments. Delivering the educational components and supervised exercise sessions directly at the worksite enhances accessibility and ecological validity, while the app-guided home-exercise program facilitates continuity and adherence. This integrated onsite and home model aligns with contemporary models of occupational health promotion and has the potential to mitigate symptoms, improve functional capacity and strengthen workers’ self-management skills.

The aim of this study is to examine the changes associated with an eight-week multimodal program (combining onsite health education workshops and supervised exercise with a home-based app-supported exercise intervention) on musculoskeletal pain, physical function, psychosocial outcomes, work ability and productivity among textile workers with WMSD, using a pre–post quasi-experimental design.

By integrating workplace-based education with supervised and app-guided exercise, this study seeks to provide a feasible and scalable approach to reduce the burden of musculoskeletal disorders in industrial settings. Based on current evidence on multimodal interventions and digital health support, we expect that participation in the program will be associated with reductions in musculoskeletal pain and improvements in physical function, psychosocial outcomes, work ability and productivity at post-intervention and follow-up assessments.

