### Secondary outcomes

2.7

*Musculoskeletal symptoms:* Musculoskeletal symptoms will be assessed using the Standardized Nordic Musculoskeletal Questionnaire (NMQ) developed by Kuorinka et al. (19) This questionnaire assesses the presence of pain or discomfort in nine body regions (neck shoulder, elbows, wrists/hands, upper-back, hips/thighs, knees and ankles/feet). Participants will indicate whether they have experienced musculoskeletal symptoms in each body region during the preceding 12 months and the preceding 7 days, and whether these symptoms have resulted in limitations in normal work activities.

The NMQ will allow the assessment of the prevalence, anatomical distribution, and work-related functional impact of musculoskeletal symptoms in this occupational population, as well as their changes following the intervention. The Spanish version of the NMQ has demonstrated adequate reliability and content validity, supporting its use in Spanish-speaking working populations (20, 21).

*Muscle strength:* Upper-limb muscle strength will be assessed using a handgrip dynamometer (Takei Grip-D dynamometer) to measure maximal handgrip force (kg), following standardized testing procedures. Participants will perform the test in a seated position with the elbow flexed at 90°, and the highest value of three trials will be recorded.

Handgrip strength is a reliable and valid indicator of general muscle strength and functional health, and it has been extensively used in occupational and clinical populations (22, 23). Reference values adjusted for age and sex will be used for interpretation. The test demonstrates excellent test–retest reliability and concurrent validity, with high intraclass correlation coefficients reported across populations.

*Functional Capacity:* Functional capacity will be evaluated using the 30-s Sit-to-Stand test which quantifies the number of complete sit-to-stand repetitions performed within 30 s. This measure serves as an indicator of lower-limb strength and functional ability associated with everyday and work-related tasks. The 30s STS test is a commonly used, valid and reliable measure of lower extremity strength and functional performance in populations with chronic musculoskeletal pain and working-age adults.

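### Thirteen secondary scores are each judged at p < 0.05 with Bonferroni only across visits, while the hypothesis draws conclusions from them and no text calls them exploratory

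*Protocol article*

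**What the plan says.** **Threshold and correction (protocol article, section 2.10).** The significance rule is "Statistical significance will be set at *p* < 0.05", with no distinction between primary and secondary outcomes. In the parametric branch, "a repeated-measures ANOVA will be conducted, with post-hoc pairwise comparisons adjusted using the Bonferroni correction". In the non-parametric branch the Friedman test is followed up "with post-hoc pairwise comparisons conducted using Wilcoxon signed-rank tests, and *p*-values adjusted using the Bonferroni correction". In both branches the correction covers comparisons between visits within one outcome.

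**Primary outcome (section 2.6.2).** One contrast is named: "The primary outcome will be the change in NRS scores from baseline to post-intervention".

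**Reach of the secondary outcomes.** The closing paragraph of the Introduction expects "reductions in musculoskeletal pain and improvements in physical function, psychosocial outcomes, work ability and productivity at post-intervention and follow-up assessments". Section 3.1 says that the set of measures "allows a comprehensive evaluation of intervention effects beyond pain alone".

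**Status of the secondary tests.** No section orders them, makes them conditional on the primary result, or calls them exploratory. Only the process and feasibility indicators in section 2.7.1 are described as descriptive.

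**The concern.** The plan does address multiplicity. It chooses a correction and sets its scope, but covers only the smaller source (three visit pairs) and leaves out the larger one (many outcomes). A reader who sees Bonferroni named may take the matter as settled.

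This matters because the secondary outcomes are meant to carry conclusions. The hypothesis lists four domains beside pain, at two time points. If the plan is followed exactly, one p < 0.05 among sleep, mood, strength, work ability or productivity scores could be read as support for that hypothesis, although chance alone produces such a result much more often than 5% of the time.

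**Working it through.** **Step 1. Count the scores named in sections 2.7 and 2.7.1.**

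| Instrument | Scores |
|---|---|
| Handgrip | 1 |
| 30-s sit-to-stand | 1 |
| IPAQ-SF (MET-minutes/week) | 1 |
| WAI total | 1 |
| PSQI global | 1 |
| DASS-21 subscales | 3 |
| EQ VAS | 1 |
| WPAI | 4 |
| **Total** | **13** |

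An EQ-5D index would make 14, but the article does not name one. The Nordic questionnaire (NMQ) is left out of the count because no test of it is specified.

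**Step 2. The plan's own figure.** The article gives no error rate across outcomes. Its only figure is the per-test 0.05, which is also the overall rate when there is a single test: 1 − 0.95¹ = 0.05. That is the position of the primary outcome.

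**Step 3. Thirteen independent tests, no true change.**

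- Chance of at least one p < 0.05: 1 − 0.95¹³ = 0.487. With 14 scores: 1 − 0.95¹⁴ = 0.512.
- Expected number of false positives: 13 × 0.05 = 0.65.

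**Step 4. Correlated tests.** The article gives no correlations between outcomes, so these are assumptions. Simulating 13 equally correlated normal test statistics, two-sided at 0.05, gives 0.33 at correlation 0.5 and 0.19 at 0.8.

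**Step 5. The procedure as written.** Simulation with n = 27 (the evaluable number in section 2.9), three visits, normal data, equal correlation between visits and no true change. Each score gets a repeated-measures ANOVA at 0.05 and three paired comparisons at 0.05/3 = 0.0167. A score counts only if the omnibus test and at least one adjusted pair are both significant. In the favourable row, the significant pair must be an improvement from baseline to post-intervention or to follow-up.

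| Chance of at least one false result among 13 scores | Independent | Correlation 0.5 | Correlation 0.8 |
|---|---|---|---|
| Any p < 0.05 (steps 3 and 4) | 49% | 33% | 19% |
| Omnibus and adjusted pair, any direction | 39% | 26% | 17% |
| Omnibus and adjusted pair, favourable from baseline | 16% | 10% | 7% |

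The last two rows carry simulation error. A repeat run agreed to within about two percentage points.

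**Step 6. What the visit-level Bonferroni achieves.** Comparing the first two rows, it lowers the any-direction rate from 49% to 39% (independent) or from 33% to 26% (correlation 0.5). It does not bring the rate across outcomes near 5%, and was not designed to.

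**The case against.** **One primary outcome is named and the study is sized on it.** Section 2.6.2 fixes the contrast, section 2.9 computes the sample size for pain alone, and Table 2 labels everything else secondary. Unadjusted secondary outcomes beside one primary are common. This stands: the primary error rate is not affected. It does not answer the point that the hypothesis and section 3.1 plan conclusions from the secondary outcomes.

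**A condensed article may leave this to an analysis plan.** That would answer a silence. Section 2.10 is not silent: it sets the threshold for all outcomes and states where the correction applies.

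**The article is cautious elsewhere.** It speaks of associated changes, calls the study a preliminary evaluation, says that the design limits causal inference, and reports effect sizes and confidence intervals with p-values. This reduces the harm. But those statements concern the absence of a control group, not the number of tests, and none sets the status of the secondary tests.

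**The rates assume no true change in any secondary outcome.** Correct. In an uncontrolled design, real but non-causal change is also possible, and no multiplicity rule protects against that.

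**Two stronger readings are tempting and not supported.**

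- A reader might infer that every NMQ item is tested as well, since section 2.7 gives "This questionnaire assesses the presence of pain or discomfort in nine body regions" and three questions for each, or 9 × 3 = 27 items. But section 2.10 opens with "The statistical analysis of the quantitative data will be performed using IBM-SPSS Statistics version 29" and names no test for binary items, and no section says that the items are tested one by one. NMQ results would add to the error, but by an amount the article does not allow to be computed.
- A reader might infer that a false claim of benefit is likely. The any-direction rates include worsening. For a favourable change from baseline under the written procedure, the chance is about 7% to 16%: above 5%, but not likely.

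**Conclusion.** The concern holds in limited form. Section 2.10 controls error across visits but not across outcomes, while the hypothesis and section 3.1 plan conclusions from outcomes whose tests are neither gated nor labelled exploratory. Among the 13 named scores, the chance of at least one false p < 0.05 is about 19% to 49%. Under the full written procedure it is about 17% to 39% in any direction, and about 7% to 16% for an apparent improvement from baseline. The figures rest on no true change in any score, assumed equal correlations from 0 to 0.8, and for the procedure normal data with 27 evaluable participants. The conclusion on pain from baseline to post-intervention does not depend on any of this. The change is worth making, but the point does not threaten the primary analysis.

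**What to change.** In section 2.10, state that the confirmatory conclusion rests only on the change in NRS from baseline to post-intervention. State that all secondary outcomes and all comparisons involving the one-month follow-up are exploratory, are reported as estimated changes with 95% confidence intervals, and support no claim of effect from p < 0.05 alone. Reword the hypothesis in the Introduction so that pain is the hypothesis and the other domains are exploratory.

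This takes a few sentences and no extra participants or data. It is best done before results are known, because a later exploratory label is less convincing. The price is that an isolated significant secondary result can no longer be presented as an effect of the programme.

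If the sponsor wants to claim a secondary effect, a small set of scores named in advance and adjusted for multiplicity would allow it; this is optional. Bonferroni over every score would be costly: with 14 scores the level is 0.05/14 = 0.0036, and at n = 27 and a standardised change of 0.60 the power of a paired t-test falls from about 85% to about 48%.
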